## Abstract

**Background:**

Frequent HIV testing among people at high risk of HIV infection is critical for early diagnosis and prompt antiretroviral therapy (ART) initiation for those who test HIV positive, as well as provision of effective biomedical HIV prevention modalities like pre-exposure prophylaxis (PrEP) for those who test negative. Despite World Health Organization (WHO) guidelines recommending retesting for HIV every 3–6 months for adults at increased risk**,** regular retesting is infrequent in sub-Saharan Africa. Large-scale, multi-arm field experiments (“megastudies”) can evaluate many different behavioral interventions among the same population and at the same time rapidly identify behavioral solutions and overcome the challenge of comparing results across standalone trials. We describe the protocol for a megastudy that will simultaneously test multiple low-cost behavioral interventions to increase HIV retesting among adults at high risk of HIV infection in rural Kenya and Uganda.

**Methods:**

We will conduct a 12-arm randomized trial of light-touch (“nudge”) behavioral interventions among 30,000–40,000 HIV-uninfected adults aged ≥ 15 years in western Kenya and southwestern Uganda who self-report increased risk of HIV infection and have access to a mobile phone. Following a baseline HIV-negative test at a high-volume HIV testing center, participants will be individually randomized in parallel to one of 12 arms, including 10 different intervention arms comprising low-cost messages that serve as nudges for retesting, an intervention arm with a financial incentive for retesting, or a control arm with standard of care post-test counseling services. The primary outcome will be HIV retesting at any study venue 3–6 months after the initial baseline HIV test. We will also measure HIV-positivity, linkage to care and ART initiation, and PrEP referral acceptance at follow-up.

**Discussion:**

This study will provide new information on low-cost interventions to promote HIV retesting for adults at elevated risk of infection in East Africa. The methods and results of this study will provide valuable insights for those engaged in HIV service delivery and influence how researchers and programs design and test low-cost, scalable interventions to promote health behaviors.

**Trial registration:**

ClinicalTrials.gov NCT06971367. Registered on May 6, 2025, https://clinicaltrials.gov/study/NCT06971367

## Introduction

### Background and rationale

Frequent HIV testing among people at increased HIV risk is crucial for epidemic control. For those who have recently become infected, frequent testing is critical for early diagnosis and prompt antiretroviral therapy (ART) initiation, thus reducing morbidity and eliminating HIV transmission risk [1–3]. For those who are HIV-negative but remain at higher risk of HIV infection, retesting enables provision of effective biomedical HIV prevention modalities like pre-exposure prophylaxis (PrEP). World Health Organization (WHO) guidelines recommend retesting every 3–6 months for adults at increased HIV risk [4].

Despite WHO guidelines, regular retesting is infrequent in sub-Saharan Africa (SSA) and results in delayed HIV diagnosis following infection. Several surveys show that many adults have not had an HIV test in the prior year [5–7] and that the median time to HIV diagnosis following infection remains > 2.5 years even as the proportion of adults who have ever tested for HIV increases [8]. Global estimates of CD4^+^ cell count at HIV diagnosis and ART initiation are unacceptably low, with ~50% of people starting ART globally at CD4^+^ counts < 350 cells/μL in studies from the 2010s [9, 10]. Late diagnosis results in missed opportunities for HIV treatment as prevention along with avoidable morbidity and mortality [1–3].

Behavioral barriers to HIV retesting are distinct from barriers to one-time testing. In a study among adults in southwestern Uganda at increased risk of HIV recruited from bars, sites of commercial sex work, and transport hubs, we found that although most adults (> 80%) reported ever testing for HIV, few (18%) reported regular retesting for HIV every 3 months in accordance with Uganda guidelines [11]. Similar findings have been reported elsewhere in SSA [12–14]. The factors driving low retesting rates include low perceived HIV risk based on a prior HIV-negative test result [15], inaccurate mental models of HIV infection (e.g., the belief that retesting is unnecessary if a person continues to feel healthy [16, 17]), and decreased salience of or focus on prevention over time (i.e., prevention fatigue) [18, 19].

In a wide range of settings, behavioral science research has demonstrated the potential for addressing barriers to various health behaviors with low-cost interventions, including “nudges” that encourage specific actions without restricting choices [20, 21]. These include messages that frame health information in salient ways and leverage behavioral economic patterns (e.g., by leveraging status quo bias through the use of default appointments) [22]. Such interventions have shown promise in promoting many health behaviors, but they have seldom been applied to retesting. Moreover, since individual behavioral interventions to increase re-testing have been evaluated in different settings, populations, and time periods, it is difficult to make like-to-like comparisons across retesting interventions and select the one most likely to boost retesting rates for implementation.

Large-scale, multi-arm field experiments (sometimes referred to as “megastudies”) that feature individual randomization and evaluate many different behavioral interventions among the same population and at the same time can rapidly identify behavioral solutions and overcome the challenge of comparing results across standalone trials. In recent megastudies, researchers have sought to identify solutions for public health priorities in the USA like exercise and flu vaccination uptake in large populations (from 30,000 to 3.1 million persons) [23–26]. Such trials make it possible to test the efficacy of *many*interventions in the same population for the same outcome [27]. This approach also increases the speed and reduces the cost with which we learn about each intervention, thus accelerating scientific discovery.

There are few evidence-based interventions to promote retesting for HIV among high-risk persons. A recent systematic review of interventions to promote retesting found ten studies (only three of which were in SSA) and reported that text message reminders were most effective [28]. In a recent trial we conducted in Uganda, small financial incentives significantly increased retesting 3 and 6 months after a negative test among adults at increased risk of HIV [29]. In the present trial, we will leverage the megastudy approach to adapt, test, and compare multiple low-cost behavioral interventions to increase HIV retesting among adults in rural Kenya and Uganda.

## Methods

### Objectives

The Innovative Behavioral Intervention Strategies (IBIS) megastudy is designed to determine the effectiveness of multiple behavioral interventions to promote HIV retesting among adults at increased risk of HIV infection. The study will also estimate heterogeneous treatment effects to determine which interventions are most effective for priority sub-populations such as youth populations and individuals with multiple sex partners.

### Trial design

We will conduct a 12-arm randomized trial of multiple behavioral economics interventions compared to a standard of care control arm. Participants will be individually randomized in parallel to one of 10 different intervention arms that offer low-cost messages that serve as nudges for retesting, an intervention arm with a financial incentive for retesting, or a control arm with standard of care HIV post-test counseling services. The financial incentive arm is intended to provide a benchmark against which the effectiveness of the other behavioral nudges can be evaluated.

### Methods: participants, interventions, and outcomes

#### Study setting

This study will take place in Homa Bay and Migori Counties in western Kenya and Bushenyi and Ibanda Districts in southwestern Uganda. Recruitment and study activities will occur in eight hospitals and clinics that provide HIV testing services (HTS) as well as HIV prevention (e.g., pre-exposure prophylaxis (PrEP)) and antiretroviral therapy (ART) services. Specific hospitals and clinics were selected based on the number of adults who accessed HTS in recent years, thereby leveraging existing high-volume testing service infrastructures to provide a sufficient population base for the study.

#### Eligibility criteria

Individuals who undergo HIV testing at study-associated health facilities will be screened for the following eligibility criteria: age ≥ 15 years, negative HIV antibody test result at time of enrollment, no intent to migrate out of the community in the next 3 months, daily access to a mobile phone, and self-reported increased risk of HIV infection (defined by national (Kenya or Uganda) MoH criteria [30, 31]). Access to a mobile phone is a requirement because some of the interventions will be reinforced by SMS messages in the 3 months after enrollment. 

#### Ethics and consent

Because of the minimal risk associated with the behavioral interventions, we will obtain verbal informed consent from participants prior to enrollment in the study. All informed consent procedures will be conducted by trained research assistants and HTS counselors in Kiswahili or Dholuo in Kenya, Runyankole or Luganda in Uganda, or English (both countries), based on the participant’s preference. Consent will be obtained by trained research assistants and Ministry of Health (MoH) counselors. The study protocol, informed consent and procedures have been approved by the University of California, San Francisco Institutional Review Board (UCSF IRB), the Makerere University School of Medicine Research and Ethics Committee (SOMREC), and the Kenya Medical Research Institute Scientific and Ethics Review Unit (KEMRI-SERU). If there are any protocol amendments affecting study participation or informed consent, those will be shared with enrolled participants at their follow-up visit.

#### Random allocation

After eligibility is determined and the baseline questionnaire is completed, enrolled participants will be randomized to one of the 12 study arms using parallel group randomization, stratified by sex and by study site, using a computer-generated sequence with permuted blocks of size 36. Study arm allocation will be revealed to participants and research assistants (RA) on the study tablet, which will display a digital rotating wheel. Participants may choose when to stop the wheel’s rotation by clicking or requesting the RA to click a “stop” button, which will then reveal the randomization study arm assignment within the relevant stratum. The data analyst generated these random allocation sequences in advance, and RAs who assign participants to the interventions will not have access to the random allocation sequence.

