### Sample size

We made the following assumptions in determining the sample size and minimum detectable effect sizes. With 64,000 adults (≥ 15 years) testing for HIV in 2023 at the eight study HIV testing service sites and a reported HIV positivity of ~ 2%, we estimate there are about 62,700 HIV-negative adults tested per year in these study communities. We estimate that about 50% of adults (about 31,000/year) accessing HIV testing at HIV clinic sites will be classified as being at increased risk of HIV infection based on their self-reported answers to risk screening questions and thus will require quarterly HIV retesting. Based on our prior HIV retesting studies in Uganda, we anticipate at least 90% of eligible adults will agree to participate in the megatrial [29, 32]. With enrollment over 18–24 months, we anticipate enrolling 30,000–40,000 participants in the trial, with a range of 2500–3333 participants per arm in a 12-arm trial.

Based on our previous retesting study in Uganda, we assumed that 38% of the control group will retest for HIV within 6 months [29]). With a sample size of at least 3000 participants/arm, we will have 80% power to detect a 4.7 percentage-point difference in HIV testing for any of the intervention groups compared to the control group. These power calculations account for multiple hypothesis testing by using a Bonferroni correction and setting the significance level to 0.00455 (i.e., 0.05/11 comparisons between interventions and control). This is a very conservative approach; however, since we will have more statistical power in our analyses by using the Benjamini and Hochberg Procedure to control the false discovery rate [41] and covariate adjustment will also improve efficiency. Thus, in practice we expect to be able to detect differences between each intervention group and the control group that are smaller than 4.7%.

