### Blinding and limitation of risk of bias

Given the nature of the study and intervention procedures, blinding is not possible for study staff nor participants. The principal investigators, co-investigators, and statistician will remain blinded to the study arm allocation of participants through the course of fieldwork and primary outcome analysis.

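### One fixed, published block size of 36 in an open trial leaves allocation only partly concealed, mainly for contrasts with the cash-incentive arm

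*Protocol article*

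**What the plan says.** Random allocation (protocol article) describes allocation to the 12 arms as "stratified by sex and by study site, using a computer-generated sequence with permuted blocks of size 36". The same section says "Study arm allocation will be revealed to participants and research assistants (RA) on the study tablet". Its concealment safeguard is that "RAs who assign participants to the interventions will not have access to the random allocation sequence".

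Blinding and limitation of risk of bias: "blinding is not possible for study staff nor participants". Ethics and consent: "All informed consent procedures will be conducted by trained research assistants and HTS counselors". So the group that sees assignments also enrols.

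Study setting: "Recruitment and study activities will occur in eight hospitals and clinics". Sample size implies equal allocation, "with a range of 2500–3333 participants per arm in a 12-arm trial". Trial status puts the start of enrolment at December 9, 2025 and its expected end in June 2027.

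**The concern.** A hidden list is enough only if the next entry cannot be inferred. Here the block size is constant and public, every assignment is visible at the site, and the strata are just site and sex, so staff know which sequence the next person will draw from. A running count then shows which arms are used up in the current block.

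The arm that staff or participants have most reason to care about is the one that pays cash. It is easy to recognise, because the counselor announces it at baseline. Some eligibility items (reported risk, migration plans, daily phone access) rest on answers taken before allocation, so there is some room for judgement before a person is committed.

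If people likely to return were favoured while a cash place was still possible, or passed over once none was, the incentive arm would differ from the others at baseline. The article uses that arm as the benchmark for the nudges. A large sample does not shrink a bias of this kind.

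**Working it through.** **Inputs.** Block size 36, 12 arms, strata of sex by site (Random allocation); 8 sites (Study setting); 30,000–40,000 participants, equal arms, 3,000 per arm for the power statement (Sample size).

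**The plan's own figure.** For 38% versus 42.7% at alpha 0.05/11 = 0.00455 (taken as two-sided) and 80% power, the requirement is 2,949 per arm; 3,000 per arm gives power 0.809. The stated power is reproduced and does not depend on the block scheme.

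**Block structure.** 36/12 = 3 places per arm per block. 8 × 2 = 16 strata. 30,000/16 = 1,875 and 40,000/16 = 2,500 people per stratum, or about 52 to 69 blocks each.

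The next results are for an observer who knows the block size and boundaries and has a complete tally for the stratum.

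**Places known with certainty.** The last place is always certain. With two left, the next is certain if both belong to one arm (probability 2/35); with three left, if all three do (2/35 × 1/34).

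- Expected number per block: 1 + 0.0571 + 0.0017 = 1.059.
- Share: 1.059/36 = 2.9%. At 36,000 participants (1,000 blocks) that is about 1,060 assignments.

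**Places after the cash arm is used up.** The 3 cash places split the other 33 into 4 gaps of equal expected length.

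- Expected number in the last gap: 33/4 = 8.25.
- Share: 8.25/36 = 22.9%, or about 8,250 of 36,000.

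**Cash certain to be next.** 3/36 + (3 × 2)/(36 × 35) + (3 × 2 × 1)/(36 × 35 × 34) = 0.0833 + 0.0048 + 0.0001 = 0.088 places per block, about once in 11 blocks.

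**Best guess.** Over 100,000 simulated blocks, guessing the arm with most places left is right for 7.26 of 36 places (20.2%), against 3 of 36 (8.3%) by chance. By position: sixth-last 28%, third-last 39%, next-to-last 53%, last 100%.

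**Which contrasts are exposed.** A given place in any non-cash arm comes after all three cash places with probability 1/4, because it is equally likely to hold any rank among the four. This is the same for control and for each messaging arm. Enrolment steered only on the cash tally therefore shifts those 11 arms equally in expectation. No cash place can fall in that stretch, so the incentive arm is not shifted.

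Let d be the difference in retest propensity between people enrolled after the cash arm is used up and people enrolled before. The bias in an incentive contrast is then about 0.25 × d in size. The article gives no d, so these are illustrative assumptions:

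| d (percentage points) | Bias, all enrolment affected | Bias, 10% affected |
|---|---|---|
| 5 | 1.25 | 0.13 |
| 10 | 2.5 | 0.25 |

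For scale, the design difference is 4.7 points.

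**The case against.** The case for leaving the scheme alone has weight. A block of 36 is long, and the useful inferences need a known block boundary and a tally pooled over everyone enrolling at a site, in two interleaved sex strata. The article does not say how many assistants or tablets a site has, or whether staff are told the block size. It is a condensed account, and operating procedures not shown may cover this. The tablet withholds the baseline survey until eligibility and consent are recorded, and allocation follows the survey, so any steering must happen before consent. Demographics and risk factors are recorded before allocation, and the Sample size section expects covariate adjustment, so selection on measured factors would be visible and partly adjustable. All of this stands, and it limits the importance of the point. It does not restore concealment: the tablet lock fixes the order of steps, not what staff know when they approach or screen someone, and adjustment cannot be relied on for unmeasured likelihood of returning.

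A reader might infer three stronger things. One is that late-block assignments can be worked out; only about one place in 36 is certain, and cash is almost never certain to be next. Another is that every arm contrast is biased; steering on the cash arm leaves messaging and control exchangeable. Control is known to be used up just as often (22.9%), but the article suggests no motive for steering on it. The third is that staff do choose whom to enrol next on this basis; the article says only that people tested at the facilities are screened.

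**Conclusion.** The point holds as a modest, avoidable weakness in concealment. Hiding the list does not fully conceal allocation when one published block size is used and the enrolling staff see each assignment. The inference that occurs often is negative: for about 23% of assignments the cash arm is known to be unavailable. Incentive-versus-control and incentive-versus-messaging contrasts are the ones mainly exposed.

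The percentages assume known boundaries and a complete tally, so they are upper limits on what site staff could know. Whether staff have that knowledge, and how much selection would follow, cannot be derived from the article. Nothing here shows that selection has occurred, and the sample size and power statement are untouched.

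**What to change.** For sequences not yet used, generate randomly varying block sizes that are multiples of 12 (for example 36, 48 and 60, giving 3, 4 or 5 places per arm) within the same site-by-sex strata, and load them into the existing tablet system. Having seen three cash assignments, an observer could then no longer be sure that none remains. Keep the new sizes from site staff and out of public text until enrolment closes, since the gain is smaller against anyone who knows the set of sizes.

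For participants already enrolled under fixed blocks, compare baseline characteristics by position in block. This needs no arm labels, so it does not disturb the blinding of investigators and statistician. It can detect only selection on measured characteristics.

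Cost: regenerating the unused part of 16 computer-generated lists, replacing live lists at eight sites during enrolment, a short amendment through the ethics bodies, and slightly looser balance within strata, which is negligible at 1,875 to 2,500 people per stratum. No extra participants or study procedures are needed.

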#### Interventions

##### Intervention selection and adaptation

Based on our prior work evaluating interventions to promote HIV retesting [11, 29, 32], as well as a literature review of low-cost behavioral economic nudges, we identified eight initial candidate interventions designed to address the psychological underpinnings of barriers to HIV retesting. We also invited 36 researchers with expertise in behavioral economics, HIV testing, and HIV prevention in East Africa to propose additional behavioral interventions for consideration. All suggested interventions were reviewed by study investigators from the United States, Kenya, and Uganda for the HIV retesting barrier being addressed, the behavioral economics underpinning theory, prior evidence of effectiveness for other health behaviors, and feasibility for the IBIS study. Investigators individually reviewed and scored each submission and then met as a group to select which intervention ideas would proceed to local adaptation. From 23 suggested intervention ideas, we selected 11 interventions for adaptation. Recognizing that many promising interventions often fail because of inadequate adaptation to local context, we undertook a two-part adaptation process for candidate interventions prior to implementing them in the study: participatory prototyping workshops in both Kenya and Uganda and a pilot trial of the updated interventions at study sites.

We recruited two groups of individuals for the participatory prototyping workshops: (1) community members aged ≥ 18 years, self-reported being HIV-negative, and self-reported at least one of the following HIV risk factors in the previous 3 months: having had more than one sexual partner, having a known HIV-positive partner, having been diagnosed with a sexually transmitted infection (STI), and/or having paid or received gifts or money in exchange for sex; (2) health care workers (HCWs) such as clinical officers, nurses, or doctors who deliver HTS at Ministry of Health (MoH) clinics. Participants provided written consent, including consent to be audio recorded, prior to the start of the workshops.

We engaged workshop participants in one full day of intervention prototyping activities, conducted in the local language by facilitators from the Busara Center, a nonprofit organization based in Nairobi, Kenya with experience in conducting behavioral science and behavioral design research in low and middle-income countries. We divided participants into groups (4–8 participants each), each of which reviewed 2–4 prototype interventions and provided structured feedback on the appropriateness and acceptability of the content, language, and framing for intervention baseline videos and SMS follow-up messages. The Busara team recorded, transcribed, and coded the user experience discussions and distilled feedback on the interventions into a report for the study team.

Following workshop completion, we implemented a small-scale pilot study in each of the eight study communities to gain additional insights on intervention acceptability and delivery and further de-risk our trial. All participants provided written consent prior to enrollment in the pilot trial. Eligibility criteria and study procedures for the pilot study matched those of the study, listed below. We used participant feedback from the workshops and pilot study to revise and finalize 10 messaging intervention scripts for use in the study.

